## **5.4 END OF STUDY**

The end of the study is defined as the last patient last visit.

## 6. STATISTICS AND DATA ANALYSIS

### 6.1 Sample size calculation

We have undertaken the most contemporary evidence synthesis, including data from 27 trial arms. Across 10,187 participants, EDPTP alone was associated with a DVT rate of 10.97%. With respect to EDPTP in addition to GCS, pooling 651 participants, the rate of DVT was 7.37%. The rate of PE in the literature is low, 0.05–0.11% and hence is unlikely to influence the sample size. These estimates are based largely on orthopaedic studies, 17 of the 27 study arms. The rate of DVT post major abdominal surgery and gynaecology oncology surgery tends towards to 5% (37, 38).

From search of NHS England Hospital Episode Statistics (HES) treatment episode we know ~80% of eligible participants will be undergoing orthopaedic joint replacement surgery, and hence the event rate will be closer to our summation analysis(26). The remaining 20% of cases will be from general and gynaecological cancer surgery. Hence, when accounting for these proportions, we anticipate the observed rate of VTE to lie close to 8%.

For 90% power at a 1-sided 2.5% level of significance, the study requires an unadjusted sample size of 7,736 to detect a non-inferiority margin of 2%, assuming the standard of care (EDPTP and GCS) DVT rate at 90 days is 8%. Following the same design as the NIHR/HTA funded GAPS study we will use a group sequential design with 2 scheduled interim analyses (at 40% and 65%, and a final analysis, at 100%, if not stopped early) to provide flexibility to stop early for overwhelming evidence of effectiveness or for futility. We will use an asymmetric 2-sided nonbinding Hwang-Shih-DeCani spending function, and this inflates the sample size to 8,264.

From GAPS, we know 4% of participants had a missing primary outcome, so we have adjusted the maximum expected sample size up to 8,608.

The non-inferiority margin has been set to 2%. Historically, VTE rates in the absence of treatment (i.e., no GCS or pharmacological thromboprophylaxis) were as high as 40% for joint replacement and 13% for abdominal and pelvic surgery. We have assumed an 8% VTE rate for standard of care (EDTPT in addition to GCS) and a 2% non-inferiority margin. Hence, the established benefit is  $40-8=32\%$ . We will preserve  $(32-2)/32$  or 94% of the established benefit, with  $>2\%$  representing a clinically meaningful difference by consensus from the expert opinion of the clinicians, and the patients.

## 6.2 Statistical analyses

Statistical analysis will be governed by a comprehensive SAP written by the study statistician and agreed by the independent Trial Steering Committee (TSC) and independent Data Monitoring Committee (iDMC) before any unblinded data is seen.

Main analysis will be according to intention-to-treat principle and will compare rates of VTE at 90 days, adjusting for any pre-specified strongly prognostic baseline covariates using a mixed effects logistic regression with study site as a random effect and pre-specified baseline covariates strongly related to outcome being used to adjust the estimated treatment effect. Primary outcome will be VTE at any time up to 90 days. The findings will be assessed for robustness against any missing data, first using multiple imputation assuming this data is missing at random and, if appropriate and the data permits, further sensitivity analyses will be attempted under any plausible missing data mechanisms not missing at random. In particular, since for non-inferiority designs, in which the null hypothesis is that the randomised groups differ, the intention-to-treat analysis may not be the most conservative, and so we will conduct a suitably specified Per Protocol analysis (defined by adherence to study protocol) as a supporting analysis to the main ITT analysis. We will also include a time to event specification (a Fine & Gray) model of the primary endpoint to check on the influence of any competing risk of death (expected to be a rare event at  $\sim 1\%$  overall). Secondary

outcomes will be analysed in a similar fashion with generalised linear models appropriate to the distribution of the outcome. Safety data will be summarised descriptively. An additional sensitivity analysis of NHS-only patients (including patients referred by their GPs to non-NHS sites) will be conducted to ensure generalisability to a NHS population.

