## 5.1.2. INTERVENTION

Participants randomised to the intervention arm will receive EDPTP alone (no GCS during the admission).

Extended duration pharmacological thromboprophylaxis is the practice of prescribing the thromboprophylaxis for a duration after hospital discharge. Prevention of DVT is a licenced indication and recommended by NICE guidelines [NG89] for several Low molecular weight heparins (LMWH) such as Tinzaparin, Enoxaparin, or Direct oral anticoagulants (DOACs) such as Rivaroxaban, Apixaban. Aspirin is an antiplatelet medication that reduces platelet function with a variety of clinical indications. The use of aspirin as DVT prophylaxis in orthopaedic surgery is also recommended by NICE [NG89](17). Prophylactic-dose thromboprophylaxis is prescribed at a lower dose in

comparison to clinical indications for therapeutic anticoagulation, such as in the treatment of diagnosed DVT or PE.

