## **Day 21 to 35 post procedure**

Day 21 to 35 post procedure (data collected via telephone or online survey [link to survey sent via email or SMS])

- VTE outcome (participants will be asked to report on whether or not they have been diagnosed with a DVT or PE since last contact)
- Adverse events associated with GCS will be captured (for those enrolled in the control arm)
- Participant reported adherence to GCS (for those enrolled in the control arm)
- Adherence to EDPTP
- Participants will also undergo a bilateral full lower limb (groin to ankle) deep venous thrombosis scan at 21- 35 days post-intervention to identify asymptomatic DVT

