## Appendix 1. Summary of investigations, treatment and assessments

| Assessment                                                                        | Days of assessment     |                      |   |          |    |
|-----------------------------------------------------------------------------------|------------------------|----------------------|---|----------|----|
|                                                                                   | Pre-surgical procedure | 0 (Day of procedure) | 7 | 21 to 35 | 90 |
| Inclusion/Exclusion                                                               | X                      | X                    |   |          |    |
| Informed consent                                                      | X                      |                      |   |          |    |
| Screening assessments                                                             | X                      |                      |   |          |    |
| Demographics                                                          |                        | X                    |   |          |    |
| Medical history (including concurrent medications)                    |                        | X                    | X | X        |    |
| Provision of leaflet explaining the signs and symptoms of developing a blood clot | X                      |                      |   |          |    |
| Provision of stockings*                                                           |                        | X                    |   |          |    |
| VTE outcome (self-reported)                                                       |                        |                      | X | X        | X  |
| A full lower limb deep venous thrombosis scan                                     |                        |                      |   | X        |    |
| Adverse Events Assessment*                                                        |                        |                      | X | X        | X  |
| Adherence to GCS*                                                                 |                        |                      | X | X        | X  |
| Adherence to EDPTP                                                                |                        |                      | X | X        | X  |

\*Patients randomised to the control arm only

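### No scheduled assessment records stocking use in the EDPTP-alone arm, so the supporting per-protocol analysis cannot reliably identify or remove contamination

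*Protocol*

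**What the plan says.** Section 6.2 makes intention-to-treat the main analysis. Because that may not be the most conservative choice for non-inferiority, it adds: "we will conduct a suitably specified Per Protocol analysis (defined by adherence to study protocol) as a supporting analysis".

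The data for such an analysis come from the contacts in section 5.3:

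- At day 7 and at days 21 to 35 the listed item is "Participant reported adherence to GCS (for those enrolled in the control arm"). The day 90 list restricts its adherence item to the control arm in the same way.
- Appendix 1 marks the row for adherence to GCS with an asterisk, explained as "Patients randomised to the control arm only".
- Adherence to EDPTP carries no such restriction in either place.

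On what each arm may wear:

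- Section 5.1.2: "Participants randomised to the intervention arm will receive EDPTP alone (no GCS during the admission").
- Section 5.1.3 lets control-arm stocking use follow local policy, which may extend beyond discharge.
- Sections 3.1 and 5.1.1 describe the intervention arm as EDPTP alone, with no time limit.

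Two general provisions apply to both arms. Section 9.1 has all protocol deviations and violations reported through the case report form. Section 8.2 has the reasons recorded when a clinician gives alternative treatment.

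**The concern.** The arms are separated by one thing, so departure from allocation has two forms: a control participant who does not wear stockings, and an EDPTP-alone participant who does. If stockings prevent VTE, both shrink the observed difference and make non-inferiority easier to declare. The per-protocol analysis is the protocol's stated answer to this, but only the first form is measured by plan.

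Crossover is possible by design. Clinicians and participants know the allocation (section 3.1), GCS with EDPTP is one of two established NHS practices (section 1.2), and clinicians may depart from allocation (section 8.2). After discharge, the planned follow-up data come from the central team's contacts, which do not put the question to this arm.

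This is not a detail that an analysis plan can settle later. An analysis plan can define a per-protocol set, but it cannot supply exposure data that were not collected.

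**Working it through.** **The protocol's own figure.** Inputs from section 6.1: 8% event rate in both arms, margin 2 points, one-sided 2.5%, power 90%.

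n per arm = (1.960 + 1.282)² × 2 × 0.08 × 0.92 / 0.02² ≈ 3,867, or 7,734 in total. The protocol states: "For 90% power at a 1-sided 2.5% level of significance, the study requires an unadjusted sample size of 7,736". This agrees within 2. Of the group-sequential design the protocol says "this inflates the sample size to 8,264", which I take as given (8,264 / 7,736 = 1.068). Allowing for 4% missing outcomes, 8,264 / 0.96 rounds up to 8,609, against 8,608 stated. The sample size is not in dispute.

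**Effect of unrecorded stocking use.** Further inputs:

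- 8,264 / 2 = 4,132 evaluable per arm (section 6.1, 1:1 allocation)
- final critical value z = 2.00 (section 6.4)
- true rates of 8% with GCS and 10% without, so the true excess sits exactly at the margin (assumption)
- a share c of the EDPTP-alone arm wears stockings and takes the 8% rate (assumption; no crossover rate is given)
- every control wears stockings, which isolates contamination
- one final look, ignoring the interim analyses

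Observed rate in the EDPTP-alone arm: p = 0.10 − 0.02c. Observed difference: d = 0.02 × (1 − c).

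SE = √[(p(1 − p) + 0.08 × 0.92) / 4,132]

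P(declare non-inferiority) = Φ((0.02 − d)/SE − 2.00)

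For c = 10%: p = 0.098, d = 0.018, SE = 0.00626. Then 0.002/0.00626 = 0.319, and Φ(0.319 − 2.00) = Φ(−1.681) = 4.6%.

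| Assumed contamination c | Observed excess (points) | SE | P(declare non-inferiority) |
|---|---|---|---|
| 0% | 2.0 | 0.00629 | 2.3% |
| 5% | 1.9 | 0.00628 | 3.3% |
| 10% | 1.8 | 0.00626 | 4.6% |
| 20% | 1.6 | 0.00623 | 8.7% |
| 30% | 1.4 | 0.00620 | 15.1% |

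Because full control wear is assumed, this approximates what remains after a per-protocol set has excluded control non-wearers. It ignores the loss of numbers and any selection from those exclusions.

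**The provisions side by side.**

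| Departure from allocation | Scheduled question? | Clearly a deviation? | Other route |
|---|---|---|---|
| Control does not wear GCS | Yes, at all three contacts | Judged against local advice (section 2.2) | Sections 8.2 and 9.1 |
| EDPTP-alone wears GCS in hospital | No | Yes (section 5.1.2) | Sections 8.2 and 9.1, if noticed |
| EDPTP-alone wears GCS after discharge | No | Unclear: section 5.1.2 names the admission only; sections 3.1 and 5.1.1 set no limit | Only if volunteered and treated as a deviation |

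**The case against.** Several points on the other side stand.

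- A reader might infer that stocking use in the EDPTP-alone arm is never recorded and that no contamination can be removed. The documents do not support that. In-hospital use contradicts section 5.1.2 and is reportable under section 9.1, and a clinician's decision to give stockings should leave a recorded reason under section 8.2. Some crossover could be found and excluded. But both routes are passive, and neither names GCS use in this arm.
- EDPTP alone, without a time limit, can be read as covering the period after discharge. Where local policy ends control stockings at discharge, a rule for the admission matches the control exposure. The mismatch arises where stockings continue at home. This is an ambiguity to resolve, not proof that later use is permitted.
- A reader might infer that crossover is likely. No figure supports this. EDPTP alone is itself an established practice (section 1.2), and Appendix 1 provides stockings to controls only.
- A reader might quote much larger error rates by adding control non-wear. With 30% of controls not wearing stockings and taking the 10% rate, the same formula gives 14.4%, 22.9% and 33.8% at 0%, 10% and 20% contamination. Those are intention-to-treat rates that start from non-wear, which is measured and can be excluded, so they do not show what the per-protocol analysis misses. Nor is the 70% adherence figure in section 3.4 an expected level: it is a pilot criterion, in days worn, at 7 days.
- Per-protocol is a supporting analysis in a pragmatic trial. That limits the severity, but it does not remove the gap.

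**Conclusion.** The point holds in a limited form. GCS use in the EDPTP-alone arm is not collected at any scheduled assessment, and its status after discharge is unclear. The per-protocol analysis can be screened systematically for control non-wear but cannot reliably identify or remove stocking use in the other arm.

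If GCS are effective, the remaining bias favours non-inferiority; if they have no effect, there is none. At a true excess of 2 points, assumed contamination of 10% to 20% roughly doubles to nearly quadruples the chance of a false declaration, from 2.3% to between 4.6% and 8.7%. These figures rest on assumed crossover shares, full protection for anyone who crosses over, full control wear and a single final look. The true crossover share may be close to zero, but the planned data could not show that.

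This should be fixed. It is not critical to the trial, because intention-to-treat is the main analysis.

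**What to change.** - At days 7, 21 to 35 and 90, ask both arms whether stockings were worn and on which days, including in hospital. Remove the control-only asterisk from the GCS adherence row in Appendix 1 and the matching restriction in section 5.3.
- Report crossover by arm.
- Have the per-protocol set take account of stocking use in the EDPTP-alone arm, counting only use before any VTE diagnosis. Excluding anyone with any use up to day 90 would be wrong: stockings worn after a diagnosed VTE would then remove events from that arm only and favour non-inferiority. The detailed rule belongs in the analysis plan, but the dates it needs must be collected now.
- Reconcile section 5.1.2 with the description of the arm in sections 3.1 and 5.1.1 and with the post-discharge stocking use that section 5.1.3 allows in controls, so that it is clear whether use after discharge counts as a deviation.

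The cost is one or two questions at existing contacts for about 4,300 participants (8,608 / 2 = 4,304), plus wording changes. Exposure is hard to recover reliably once follow-up closes, so the change is needed while data are being collected. A side benefit is that questions put to controls only reveal allocation to follow-up assessors who are meant to be blinded (section 3.1). Common questions would lessen this, although the answers may still be revealing.

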### **6.3 Subgroup analyses**

We will perform the following sub-group analyses of the primary outcome, and test for sub-group interactions if appropriate:

Predefined sub-group analyses (primary outcome) include:

- Sex (male, female)
- Age
- BMI
- Smoking status (ex-smoker, current smoker, never smoker)
- Type of anaesthesia (regional, general)

The study is not formally powered for these subgroups analyses and will be exploratory.

### **6.4 Interim analysis**

We have scheduled two unequally spaced interim analyses (at 40% and 65%) and at 100% (as a final analysis if the study is not stopped early at any of the interim analyses) to provide flexibility to stop early for overwhelming evidence of effectiveness or for futility. The z-value thresholds for futility will be 0.05 and 0.86, and for 'effectiveness' 2.90 and 2.59, with the threshold for non-inferiority at the final analysis (if reached) 2.00. Recruitment will continue while the interim data is analysed.

Full details of the stopping boundaries and analysis will be included in the SAP, which the iDMC will approve prior to seeing unblinded data. This interim analysis will be presented by the unblinded statistician at ECTU to the iDMC, who will include an

independent statistician. The unblinded ECTU statistician would have no other role in the study while it was ongoing. The stopping rules are statistically non-binding. The iDMC may recommend early stopping of the study if the boundaries are crossed. They would make a recommendation to the independent Trial Steering Committee (TSC) who may or may not endorse that recommendation. Note also that the trial can stop at any time for safety, if there is an excess of events in the intervention group that is considered to generate avoidable harm – and this would be a decision not based on any statistical criterion and taken by the iDMC and endorsed by the TSC.

For a non-inferiority design, futility corresponds to showing one or the other of the randomised interventions is superior; whereas ‘evidence of effectiveness’ is showing early that the drugs alone are indeed non-inferior to the combination.

## 7. ADVERSE EVENTS

### 7.1. DEFINITIONS

**Adverse Event (AE):** any untoward medical occurrence in a patient or clinical study subject.

**Serious Adverse Event (SAE):** any untoward medical occurrence or effect that:

- **Results in death**
- **Is life-threatening** – *refers to an event in which the subject was at risk of death at the time of the event; it does not refer to an event which hypothetically might have caused death if it were more severe*
- **Requires hospitalisation, or prolongation of existing inpatients’ hospitalisation**
- **Results in persistent or significant disability or incapacity**
- **Is a congenital anomaly or birth defect**

Medical judgement should be exercised in deciding whether an AE is serious in other situations. Important AEs that are not immediately life-threatening or do not result in death or hospitalisation but may jeopardise the subject or may require intervention to

prevent one of the other outcomes listed in the definition above, should also be considered serious.

## **7.2. REPORTING PROCEDURES**

For the purposes of the study, only AEs related to the study intervention (graduated compression stockings) will be recorded. This information will be collected at 7-days, between 21 and 35 days and at 90 days.

Safety monitoring includes any adverse events with GCS or bleeding events with the standard of care pharmacological thromboprophylaxis. Major bleeding will be defined as per the International Society on Thrombosis and Haemostasis definition (36).

Participants who report a treatment related AE which requires further investigation/follow-up will be advised to consult with their GP/relevant clinical team where necessary. Depending on the nature of the event the reporting procedures below should be followed. Any questions concerning adverse event reporting should be directed to the Chief Investigator in the first instance.

### **7.2.1 Non serious AEs**

Only AEs related to the study intervention (graduated compression stockings) will be recorded.

### **7.2.2 Serious AEs**

An SAE form should be completed and emailed to the Chief Investigator within 24 hours. However, hospitalisations for elective treatment of a pre-existing condition do not need reporting as SAEs.

All SAEs should be reported to the Research Ethics Committee where in the opinion of the Chief Investigator, the event was:

- 'related', ie resulted from the administration of any of the research procedures; and
- 'unexpected', ie an event that is not listed in the protocol as an expected occurrence

Reports of related and unexpected SAEs should be submitted within 15 days of the Chief Investigator becoming aware of the event, using the NRES SAE form for non-IMP studies. The Chief Investigator must also notify the Sponsor of all related and unexpected SAEs.

Local investigators should report any SAEs as required by their Local Research Ethics Committee, Sponsor and/or Research & Development Office.

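### Section 7 gives conflicting rules on which serious adverse events are collected, in a way that could differ by arm, and its definition of a related event does not cover the allocated omission of stockings

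*Protocol*

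**What the plan says.** Four places in the protocol bear on this point.

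- **Section 7.2** sets a general rule: "For the purposes of the study, only AEs related to the study intervention (graduated compression stockings) will be recorded". It ties that information to the follow-up contacts at day 7, days 21 to 35 and day 90. Its next paragraph extends safety monitoring to bleeding on pharmacological prophylaxis.
- **Section 7.2.1**, on non-serious events, repeats the rule: "Only AEs related to the study intervention (graduated compression stockings) will be recorded".
- **Section 7.2.2**, on serious events, states: "An SAE form should be completed and emailed to the Chief Investigator within 24 hours". The single exemption is that "hospitalisations for elective treatment of a pre-existing condition do not need reporting as SAEs". Onward reporting to the REC within 15 days, and notification of the Sponsor, apply to events that the Chief Investigator judges both related and unexpected. Related means that the event "resulted from the administration of any of the research procedures". Unexpected means "an event that is not listed in the protocol as an expected occurrence".
- **Appendix 1** stars the adverse event assessment row at all three follow-up times as applying to the control arm only.

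Sections 5.1.1 and 5.1.2 define the arms. Stockings belong to the control arm; the intervention arm receives extended pharmacological prophylaxis without stockings.

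**The concern.** Section 7 and Appendix 1 are written around harm from wearing stockings, but the strategy under test is leaving them off. Two problems follow.

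First, the scope of SAE collection is stated in two ways that do not agree. If sites act on different paragraphs, the number of SAEs and bleeding events on record depends on the site and, because one rule is tied to stockings, on the arm. Any comparison of those counts between arms would then be hard to interpret.

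Second, relatedness is defined by something being administered. An event that an investigator puts down to stockings being withheld does not fit those words. It can therefore miss the one reporting step that uses them.

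**Working it through.** The point is textual, so the check sets the provisions side by side.

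**Step 1: is an SAE an adverse event?** Section 7.1 defines both as untoward medical occurrences, the serious kind being those that meet a seriousness criterion. SAEs are therefore a subset of adverse events, and the unqualified rule in section 7.2 reaches them unless something excepts them. Section 7.2 contains no exception.

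**Step 2: what does each provision collect, by arm?**

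| Provision | Stocking arm (control) | No-stocking arm (intervention) |
|---|---|---|
| 7.2, first sentence | Stocking-related events only, serious or not | In effect none, if no stockings are worn |
| 7.2, safety monitoring | Stocking-related events and bleeding | Bleeding |
| 7.2.1 | Stocking-related non-serious events | In effect none |
| 7.2.2 | All SAEs except the elective admissions | All SAEs except the elective admissions |
| Appendix 1, adverse event row | Assessed at three contacts | Not assessed |

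Rows 1 and 4 cannot both be the scope for SAEs. Rows 2 and 5 do not fit for bleeding: section 7.2 monitors it without limiting it to an arm, but the only adverse event row in the schedule is restricted to the control arm. The visit lists in section 5.3 do not name bleeding either.

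**Step 3: naming.** Sections 7.2 and 7.2.1 call stockings the study intervention, while section 5.1.1 labels the arm without stockings as the intervention arm. The restriction is thus attached to the control-arm component.

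**Step 4: relatedness.** In the intervention arm the trial withholds something. Read literally, an SAE attributed to that omission did not result from administering a procedure, so it fails the related test. Because REC reporting needs both tests to be met, it drops out there and from the linked Sponsor notification, whatever the answer on unexpectedness.

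**Step 5: the unexpectedness test.** It refers to events listed in the protocol as expected. Section 7 has no such list and no rule for endpoint events. Whether a serious VTE would count as expected is therefore open.

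**Step 6: scale.** At the protocol's planning figures (sections 6.1 and 6.2), 8,608 / 2 = 4,304 per arm; 4,304 × 8% ≈ 344 VTE per arm; and 8,608 × 1% ≈ 86 deaths in both arms together. These give context only. They are outcomes the trial collects anyway, the VTE figure includes asymptomatic clots found by scan, and the share of VTE that would meet a seriousness criterion is not given. The number of SAEs affected cannot be derived.

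**The case against.** The strongest reply is that section 7.2, read in order, largely sorts itself out. It directs sites to the procedures that follow according to the nature of the event. The stocking restriction is repeated under non-serious events and is absent under serious events. Its link to scheduled contacts also sits badly with a form due within 24 hours. On that reading the restriction was meant for non-serious events, and all SAEs in both arms reach the Chief Investigator. This is probably what was intended. It does not remove the fault, because the sentence stands unqualified in the parent section and Appendix 1 supports the narrow reading.

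A reader might go further and infer that serious harm from omitting stockings has no expedited route or would go unseen. The protocol does not support that. Section 7.2.2 has the 24-hour form with no relatedness filter, and it separately asks local investigators to report SAEs as their own bodies require. The main foreseeable harm, VTE, is the primary outcome: section 5.3 has it asked about at three contacts and scanned for in both arms. Death is captured to day 90. Section 6.4 lets the trial stop for an excess of events in the intervention group. Nothing there says that this review relies on SAE forms, so it would be too strong to say the iDMC would be misled.

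It can also be argued that research procedures include the randomised allocation, and that the judgement is left to the Chief Investigator's opinion. That is possible, but the wording does not say it. Finally, attributing one VTE to absent stockings is hardly feasible case by case; comparing the arms answers that question. This stands, and it limits how relatedness should be widened.

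**Conclusion.** The point holds as a matter of consistency and wording, of moderate weight. The protocol states SAE scopes that conflict, and taken literally SAE and bleeding capture could differ by arm. Separately, an SAE attributed to the allocated omission of stockings falls outside the 15-day REC report and linked Sponsor notification, and only that step. This rests on reading administration literally and on section 7.2 having no exception for serious events.

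The size cannot be expressed as a count of affected events. Neither the 344 VTE per arm nor the 86 deaths measures it. The detection of VTE and death as trial outcomes is not impaired, and the sample size, alpha, power and primary endpoint are unaffected.

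**What to change.** Reconcile sections 7.2, 7.2.1 and 7.2.2 with Appendix 1:

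1. Limit the stocking-related restriction to non-serious events, in section 7.2.1, and remove or qualify the general sentence in section 7.2.
2. State that SAEs and bleeding events are collected identically in both arms, regardless of relation to stockings. Split the Appendix 1 row so that only the stocking-specific assessment is marked control arm only.
3. Word related to cover the allocated strategy, including allocation to no stockings.
4. In the same amendment, state how endpoint VTE and deaths are handled under the unexpectedness test. Making change 3 alone could turn endpoint VTEs in one arm into candidates for individual REC reports.

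The cost is a short amendment to section 7 and Appendix 1, with some additional SAE forms and causality assessments. No analysis or sample size needs to change.
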